#### Wait-list control

2.4.2

The control group will not receive any intervention for the first 4 weeks. However, for ethical reasons, the control group will be given InMind for the next 4 weeks. The MMT procedures for the control group will be the same as that for the experimental group. The experimental group will not receive any intervention while the control group will perform MMT.

### Discontinuation criteria

2.5

The discontinuation criteria for this study will include the following:

When a participant repeatedly complains of psychological or physical discomfort and wishes to drop out of the study.When a participant wishes to drop out for other reasons.

### Sample size

2.6

The minimum sample size was calculated using the G* Power program (35). A value of 0.15 indicating a small effect size and a significance level of 0.05 were set, and the power was applied as 0.80. The calculation indicated that a minimum of 90 participants is required, with a minimum of 45 participants per group. Considering a dropout rate of 20%, a maximum of 57 participants per group and a total of 114 participants will be recruited.

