### Statistical analyses

2.13

Analyses will be conducted according to the Intention-To-Treat (ITT) principle, and missing data will be imputed using the expectation maximization algorithm.

First, to investigate the effectiveness of MMT, a 2 (group: experimental vs. control) × 2 (survey time: T1 vs. T2) repeated-measures ANOVA will be performed for MBI-GS, UWES, PSS, CMAS-R, and IVS. If the interaction between the group and survey time is significant, a simple main effect analysis will be performed. Second, a paired *t-*test will be performed on MBI-GS, UWES, PSS, CMAS-R, and IVS in the experimental group to examine the follow-up effect of MMT. Third, a subgroup analysis will be performed to investigate the difference in effectiveness depending on the amount of application usage. For this purpose, 2 (subgroup: high-usage vs. low-usage) × 2 (survey time: baseline vs. post-intervention) repeated-measures ANOVA will be performed. Data from both the experimental and control groups will be used for subgroup analysis. If the interaction between the subgroup and survey time is significant, a simple main effect analysis will be performed. Fourth, a mediating effect analysis will be performed to investigate whether mindfulness and subjective vitality mediate the relationship between application use and burnout or work engagement.

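### Section 2.6 calls the target effect small, but 45 per group has 80% power only for a between-group difference of about 0.60 SD in T1–T2 change, a medium effect

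*Protocol article*

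**What the plan says.** Protocol article, section 2.6 (Sample size), names the software, "The minimum sample size was calculated using the G* Power program (35"), and the inputs: "A value of 0.15 indicating a small effect size and a significance level of 0.05 were set", and "the power was applied as 0.80". The result is given as "The calculation indicated that a minimum of 90 participants is required, with a minimum of 45 participants per group". The recruitment target follows: "Considering a dropout rate of 20%, a maximum of 57 participants per group and a total of 114 participants will be recruited".

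Section 2.13 (Statistical analyses) sets the effectiveness analysis: "a 2 (group: experimental vs. control) × 2 (survey time: T1 vs. T2) repeated-measures ANOVA will be performed", with follow-up testing conditional on the interaction of group and time.

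Section 2.6 does not name the effect-size metric, the test or the correlation between T1 and T2. It gives no target difference in MBI-GS or UWES points.

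**The concern.** Ninety participants is few for a trial said to have 80% power for a small effect. A value of 0.15 looks small as a number, but its meaning depends on the scale. For the interaction in a 2 × 2 repeated-measures design, Cohen's f is one quarter of the between-group difference in change, expressed in SDs of the outcome. A modest f therefore stands for a considerably larger treatment difference.

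What is at stake is how the trial's sensitivity is understood. As section 2.6 is worded, a reader will believe that the design can reliably detect a small benefit of the app on burnout and work engagement, the two primary outcomes.

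**Working it through.** **Inputs from the protocol.** Effect 0.15, alpha 0.05, power 0.80, 90 in total (45 per group) and 20% dropout (section 2.6); 1:1 allocation (section 2.7); two groups and two time points, with the interaction as the test (section 2.13).

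**Assumptions.** The 0.15 is Cohen's f, and the T1–T2 correlation ρ is 0.5. Neither is stated; both are inferred from the match in step 1.

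**Step 1: reproduce 90.** For the group-by-time interaction with m = 2 measurements, the noncentrality is λ = f² × N × m / (1 − ρ), on 1 and N − 2 degrees of freedom.
- N = 90: λ = 0.0225 × 90 × 2 / 0.5 = 8.10; power 0.804.
- N = 88: λ = 0.0225 × 88 × 2 / 0.5 = 7.92; power 0.795.

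So 90 is the smallest even total that reaches 80%. The other settings tried do not give 90:
- two measurements with ρ = 0.3 or 0.7: 126 or 56;
- three measurements with ρ = 0.5: 74;
- between-group F tests with one, two or three measurements: 352, 264 or 236;
- regression with f² = 0.15 and one to six predictors: 55, 68, 77, 85, 92 or 98.

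The dropout step also reproduces: 45 / 0.8 = 56.25, hence 57 per group and 114 in total.

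**Step 2: convert f to a treatment difference.** With f = 0.15, each of the four cells departs from additivity by 0.15 SD, with alternating signs. The between-group difference in change is [0.15 − (−0.15)] − [(−0.15) − 0.15] = 4 × 0.15 = 0.60 SD of the outcome. The SD of change is SD × √(2(1 − ρ)), which at ρ = 0.5 equals the outcome SD. The target is therefore also 0.60 SD of change.

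**Step 3: cross-check without ρ.** Take a two-sided two-sample t-test on change with 45 per group and a difference of 0.60 SD of change. The noncentrality is 0.60 × √(45/2) = 2.846, whose square is 8.10, and power is 0.804 as before. Expressed in SDs of change, this needs no value for ρ. Whatever was entered in the software, 45 per group reaches 80% power only at about 0.60 SD of change.

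**Step 4: power for smaller differences in change.**

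| Difference (SD of change) | f at ρ = 0.5 | Power, 45 per group | Power, 57 per group | Total N for 80% |
|---|---|---|---|---|
| 0.20 | 0.05 | 15.5% | 18.5% | 788 |
| 0.30 | 0.075 | 29.1% | 35.5% | 352 |
| 0.40 | 0.10 | 46.7% | 56.2% | 200 |
| 0.60 | 0.15 | 80.4% | 88.8% | 90 |

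**Step 5: sensitivity to ρ.** If the difference is instead fixed in SDs of the outcome, power depends on ρ. For f = 0.10 (0.40 outcome SD) and N = 90, λ = 0.01 × 90 × 2 / (1 − ρ):
- ρ = 0.3: λ = 2.57, power 35%;
- ρ = 0.5: λ = 3.60, power 47%;
- ρ = 0.7: λ = 6.00, power 68%;
- ρ = 0.8: λ = 9.00, power 84%.

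For 0.20 to 0.30 outcome SD, power runs from 13–22% at ρ = 0.3 to 32–61% at ρ = 0.8. A correlation of 0.8 is not what section 2.6 used, since f = 0.15 would then have required only 38 participants.

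**The case against.** The best defence is that the label is right on its own scale. The usual benchmarks for f are 0.10 for small and 0.25 for medium, so 0.15 lies nearer to small, and every number in section 2.6 follows from the inputs. It stands that the arithmetic is sound. The label is not rescued, because at f = 0.10 itself the design has about 47% power with 90 and 56% with 114 (ρ = 0.5).

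Other points on that side do stand and limit the finding:
- A reader might infer that power for a small effect simply is 16–29%. That range requires small to mean a 0.20–0.30 SD difference in change, which the protocol does not say.
- A reader might treat the unstated correlation as an error. An article may leave a software input to the full protocol, so its absence alone is no fault.
- A reader might conclude that a non-significant result could never exclude effects below 0.6 SD. That does not follow, because exclusion depends on the confidence interval. With 45 per group its 95% half-width is about 1.99 × √(2/45) = 0.42 SD of change. An estimate of 0 would exclude effects above about 0.42 SD, whereas a non-significant estimate of 0.40 would not exclude 0.8 SD.
- Calling 0.60 SD medium-to-large would be too strong. It lies just above the usual medium value of 0.5 and well below the large value of 0.8.
- The protocol makes no claim about how a null result would be read, so a misreading is a risk and not something the text asserts.

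**Conclusion.** The point holds as a misdescription of the effect that the trial is powered for. Section 2.6 attaches 80% power to a small effect, while 45 per group delivers it at about 0.60 SD of change. That figure depends only on the group size, two-sided alpha of 0.05 and a comparison of change between groups. Its translation to f = 0.15 and to outcome SDs rests on ρ = 0.5, the value that reproduces 90. The shortfall at the conventional small f = 0.10 is from 80% to about 47% with 90 analysed, or 56% if all 114 are analysed, again at ρ = 0.5.

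A reader might infer that 90 is miscalculated or that the trial must be enlarged. Neither follows: 90, 45, 57 and 114 all reproduce, and a trial may properly be planned for 0.60 SD if it says so.

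**What to change.** In section 2.6, delete the description of 0.15 as a small effect size and restate the calculation along these lines:

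*90 completers (45 per group) give 80% power, at two-sided alpha 0.05, to detect a between-group difference in T1–T2 change of about 0.60 SD of change (f = 0.15, assumed T1–T2 correlation 0.5); power for a 0.40 SD difference is about 47%.*

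The sponsor should confirm from its own record of the calculation that the metric was f and the correlation 0.5. Do not add a statement that a non-significant result leaves effects below 0.6 SD open; interpret a null result from the confidence interval of the difference in change.

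The change is to wording only. The sample size stays at 114, and section 3.1 says that recruitment has not started. The cost is that the stated detectable effect becomes less favourable.

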### Randomization

2.7

All participants will be randomly allocated to either the experimental or the control group. A random number table will be generated by a computer and managed by the investigator ([name]). The allocation ratio between the experimental and control groups will be 1:1. Participants will be unaware of which group they have been allocated to before enrollment. The investigator ([name]) will enroll participants in the order. After enrollment, participants will be assigned to the experimental or control group based on the random number, and other investigators will be unaware of the allocation of participants.

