#### Inclusion criteria

2.3.1

Office worker over 19 years of age.Participants subjectively complaining of stress related to various issues at work.Participants who can participate in the study for 8 weeks.

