### Blinding

2.8

Due to the nature of the intervention, both investigators and participants cannot be blinded. However, because a standardized smartphone application is provided, the threat of bias due to investigator blinding failure may be low.

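### Section 2.7 does not secure concealment of the next allocation from the person who enrols

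*Protocol article*

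**What the plan says.** Section 2.7 (Randomization) makes five statements that bear on concealment:

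- Custody of the list: "A random number table will be generated by a computer and managed by the investigator".
- Enrolment: "The investigator ([name]) will enroll participants in the order".
- Participants: "Participants will be unaware of which group they have been allocated to before enrollment".
- Timing: "After enrollment, participants will be assigned to the experimental or control group based on the random number".
- Other staff: "other investigators will be unaware of the allocation of participants".

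Section 2.8 (Blinding) then states that "both investigators and participants cannot be blinded". It argues that the resulting bias may be low because the app is standardised.

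Entry depends partly on judgement or self-declaration. Section 2.3.1 asks for "Participants subjectively complaining of stress related to various issues at work" and for ability to take part for 8 weeks, and section 2.3.2 excludes people who cannot use the application. All outcomes are self-reported (section 2.9), and the control group has no intervention for the first 4 weeks (section 2.4.2).

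**The concern.** Allocation concealment can be kept in an open-label trial, and it is the main protection against selection into arms. It requires that whoever decides that a person enters, and when, cannot know the next assignment. Section 2.7 uses one role label for holding the list and for enrolling, and its only promise about staff covers investigators other than those already mentioned. The enroller is the person from whom the next assignment most needs to be hidden, and the enroller is not clearly covered.

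If concealment fails, keener or more app-capable staff could be placed in the app arm through a soft eligibility call or through the order of entry. Such a difference would feed into unblinded self-reported burnout and engagement at T2. The group-by-time ANOVA in section 2.13 lists no covariates, and Table 2 includes no measure of motivation to practise. Once participants are allocated, the damage cannot be repaired in the analysis.

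**Working it through.** This point turns on wording, so the statements are set side by side.

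**Who is covered by the unawareness clause in 2.7.** Three readings are open:

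1. One person manages the table and enrols. The clause on other investigators then leaves out the enroller, who knows the next number. Allocations are foreseeable.
2. Two people are involved, and the clause means everyone except the list holder. The enroller is then unaware and concealment is intended, but the section does not say so.
3. Two people are involved, and the clause means everyone except those two. The enroller is again outside the promise, and foreseeability depends on access to the table.

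The clause follows the sentence on enrolment, so the most natural reading leaves the enroller out (1 or 3). Only reading 2 gives concealment, and it has to be inferred.

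**What the timing statement adds.** Assignment after enrolment is the right order, but it does not conceal anything by itself. A person who can see the list knows the next entry before the assignment is formally made.

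**2.7 against 2.8.** If the clause on other investigators means concealment up to assignment, it is compatible with 2.8 but should say so. If it means continuing unawareness of who is in which arm, it contradicts 2.8. It sits in the sentence about what happens after enrolment, so the second meaning cannot be ruled out. The argument in 2.8 from a standardised app concerns delivery of the intervention and has no bearing on selection into arms.

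**Size, as illustration only.** The documents give no steering rate and no trait effect. Assume a binary trait held by half of entrants and worth d = 0.5 SD in change, with a share s = 10% of entries steered.

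- If s is the share whose arm is chosen by the trait, trait prevalence is 0.5 + s/2 in one arm and 0.5 − s/2 in the other. The difference is s = 0.10, and the shift is 0.10 × 0.5 = 0.05 SD.
- If s is the share actually moved to the other arm, in equal numbers each way, the difference is 2s = 0.20, and the shift is 0.20 × 0.5 = 0.10 SD.

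With no steering the shift is zero, and it grows in proportion to s and d.

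For scale, section 2.6 gives f = 0.15, alpha 0.05, power 0.80 and 90 participants. Assuming a correlation of 0.5 between T1 and T2 (not stated in the protocol), lambda = 0.15² × 90 × 2 / (1 − 0.5) = 8.1. Power is then 0.804 at 90 and 0.799 at 89, so the stated 90 reproduces. For two groups of 45, lambda = d² × (45 × 45 / 90) = 22.5 d², so d = √(8.1 / 22.5) = 0.60 SD of change. The recruitment target also reproduces: 45 / (1 − 0.20) = 56.25, rounded up to 57 per group and 114 in total. The sample size is not in question here.

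**The case against.** The strongest reply is that the copy reviewed masks both names, and they may belong to two people. The duties could then already be separate, with the enroller among those kept unaware. This stands, and it is why foreseeability is stated only as a condition.

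Four further points deserve weight:

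- Enrolling in order may mean order of arrival and need not mean working down a visible list. The text does not settle this.
- Section 2.2 does not say who screens, and much of what is screened is declared by the participant. That the list holder judges eligibility or chooses the order of entry is therefore not documented.
- Consent already precedes screening (2.2), and assignment already follows enrolment (2.7). Much of the desired sequence is in place.
- Work engagement is measured at T1, so part of a motivational imbalance might show at baseline.

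It can also be said that a journal article leaves devices such as envelopes or a web randomiser to the full protocol. That is fair for the device. It does not dispose of the point, because the article does state who holds the list, who enrols and who is unaware, and that stated arrangement does not cover the enroller.

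A reader might go further and infer that one person does both tasks and that all 114 allocations are predictable. The document does not support this. It follows only if the enroller holds or can see the table, and the text neither says so nor excludes it.

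**Conclusion.** The point holds in conditional form. As written, section 2.7 does not secure concealment of the next allocation from the person who enrols, and its clause on other investigators needs reconciling with section 2.8 whoever the masked names are. Whether any allocation is in fact foreseeable depends on who holds the list and who can see it, which the copy reviewed does not show.

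The size of any resulting bias is unknown. The 0.05 to 0.10 SD above rests on assumed steering and an assumed trait effect. It is about one-twelfth to one-sixth of the 0.60 SD detectable at the planned size, a figure that itself assumes a correlation of 0.5. Severity is moderate: the illustrated bias is small beside the target effect, but it would be systematic, largely invisible in the data and beyond correction later, while prevention is cheap.

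**What to change.** Amend section 2.7 as follows:

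- State that the list is generated and held by a team member who does not recruit, screen or enrol. If the two roles are already filled by different people, say so.
- State that each assignment is released only after consent, eligibility and the T1 questionnaires are recorded and the participant is irrevocably logged as enrolled. The list holder on request, a locked web randomiser or sequentially numbered opaque envelopes would each serve.
- Replace "other investigators will be unaware of the allocation of participants" with a statement that no one who enrols can see upcoming allocations.
- Reconcile this with section 2.8 by separating concealment before assignment from the absence of blinding after it.

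The cost is protocol wording, possibly a swap of roles within the existing team, and a few minutes' delay per allocation. The sample size and the analysis are unaffected. Section 3.1 says that recruitment has not started, so the change can be in force before the first participant is enrolled.

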### Study setting

2.2

This trial will be conducted in companies and institutions in the Republic of Korea with the approval of the Institutional Review Board of Kyung Hee University. Participants will be recruited through advertisements displayed in their workplaces. People interested in participating will be gathered at a location within their workplace and informed about the study. After receiving written informed consent, they will be screened to assess the inclusion and exclusion criteria. The intervention will be smartphone-based.

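### Allocation is not described as stratified or blocked by workplace, and the T1-T2 model has no workplace term: a small, avoidable loss of precision

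*Protocol article*

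**What the plan says.** Section 2.2 places the trial in more than one workplace: "This trial will be conducted in companies and institutions in the Republic of Korea". Recruitment also runs through the employer: "Participants will be recruited through advertisements displayed in their workplaces", and interested staff are then gathered on site.

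Section 2.7 describes individual allocation. "A random number table will be generated by a computer and managed by the investigator"; "The allocation ratio between the experimental and control groups will be 1:1"; participants are enrolled in order, and after enrolment "participants will be assigned to the experimental or control group based on the random number". It mentions no stratification, blocking or minimisation.

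Section 2.6 sets the target: "a maximum of 57 participants per group and a total of 114 participants will be recruited". Section 2.13 analyses each outcome by a 2 (group) × 2 (T1, T2) repeated-measures ANOVA without a workplace factor. Section 3.1 states that recruitment has not begun.

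**The concern.** The primary outcomes are burnout and work engagement, and the Introduction itself describes work stress as partly a product of the workplace environment. Stable differences between employers cancel in the T1-T2 change. What does not cancel is change specific to one employer during the 4 weeks, such as a deadline or a reorganisation. If such change exists and the arms happen to be uneven within workplaces, part of it enters the group-by-time contrast as noise.

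As described, neither the allocation nor the model uses the workplace structure that the recruitment route creates. At stake are some power and the face validity of the comparison. A second, smaller question is how 2.7 delivers the equal arms that 2.6 counts on.

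**Working it through.** **1. The plan's own sample size.** Inputs from 2.6: "A value of 0.15 indicating a small effect size and a significance level of 0.05 were set, and the power was applied as 0.80"; minimum 90; 20% dropout. I read 0.15 as Cohen's f. The correlation between T1 and T2 is not given, so ρ = 0.5 is an assumption. For the group-by-time interaction with m = 2 occasions:

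λ = f² · N · m / (1 − ρ) = 0.0225 × 90 × 2 / 0.5 = 8.1, with df 1 and 88.

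Power is 0.804 at N = 90 and 0.795 at N = 88, so 90 is reproduced. (At ρ = 0.3 the requirement would be 126, and at ρ = 0.7 it would be 56.) For dropout, 45 / 0.8 = 56.25, rounded up to 57 per group and 114 in total, as stated. The present point does not alter these figures.

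**2. Arm sizes if the table is simple randomisation.** Binomial(114, 0.5):
- exactly 57/57: 7.5%
- arms differ by 10 or more: 40%
- smaller arm 50 or fewer: 22%
- smaller arm below 45: 1.9%

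The consequence is slight. A 50/64 split is worth 4 × 50 × 64 / 114 = 112.3 participants in balanced arms, and 1 − 112.3/114 = 1.5% is lost.

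**3. Imbalance within a workplace, with totals fixed at 57/57.** Hypergeometric probability of a 70/30 or worse split in a given workplace of assumed size n:

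| n | probability |
|---|---|
| 10 | 32% |
| 20 | 8% |
| 30 | 1.8% |
| 57 | below 0.1% |

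The chance that at least one of K equal-sized workplaces is that uneven (20,000 permutations) is 0.7% for K = 3, 10% for K = 5, 83% for K = 10 and over 99% for K = 15.

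**4. Effect on the test.** With two occasions, the interaction is a comparison of change scores. From λ = N·d²/4, the planned effect is d = √(4 × 8.1 / 90) = 0.60 SD of change. I take the workplace-by-time ICC as the share of change-score variance that lies between workplaces. Unstratified and unadjusted, the standard error is about √(4/N) = √(4/90) = 0.211 whatever the ICC. Stratified and adjusted, it is about √(4(1 − ICC)/N), which is 0.205 at ICC 0.05, 0.200 at 0.10 and 0.189 at 0.20.

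Simulated power (N = 90, 4,000 runs per setting, Monte Carlo error about √(0.8 × 0.2 / 4000) = 0.006):

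| K | ICC | as described | stratified + workplace term | workplace term only |
|---|---|---|---|---|
| 3 | 0.02 | 0.816 | 0.813 | 0.786 |
| 3 | 0.05 | 0.814 | 0.824 | 0.816 |
| 3 | 0.10 | 0.821 | 0.843 | 0.834 |
| 3 | 0.20 | 0.818 | 0.885 | 0.876 |
| 5 | 0.02 | 0.809 | 0.814 | 0.795 |
| 5 | 0.05 | 0.811 | 0.824 | 0.803 |
| 5 | 0.10 | 0.802 | 0.841 | 0.828 |
| 5 | 0.20 | 0.810 | 0.872 | 0.874 |
| 10 | 0.02 | 0.803 | 0.802 | 0.756 |
| 10 | 0.05 | 0.813 | 0.814 | 0.776 |
| 10 | 0.10 | 0.802 | 0.838 | 0.800 |
| 10 | 0.20 | 0.807 | 0.878 | 0.841 |

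In the design as described, type I error was 0.046 to 0.055, and the mean estimate was 0.595 to 0.604 against a true 0.60.

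**The case against.** The strongest reply is that individual 1:1 randomisation is valid without strata. Chance imbalance between workplaces is already covered by the standard error, and the T1-T2 contrast removes stable employer differences. This stands. A reader might infer that workplace events become confounded with treatment. The documents do not support that: workplace is independent of arm in expectation, and the simulation shows no bias and no inflated type I error. An unlucky split can shift the estimate in a single trial, but that is chance error and not a systematic one.

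Second, this is a condensed article, and block sizes or strata may be left to the full protocol. This stands in part. Section 2.7 never says that allocation is simple or unstratified, so that reading rests partly on silence. However, the section does describe a mechanism, and taken plainly it makes no use of workplace. If stratification is planned, one sentence settles the matter.

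Third, the 1:1 ratio and the cap of 57 per group fit a list with fixed totals at least as well. This stands: the 7.5%, 40% and 22% apply only under simple randomisation, and even then the efficiency loss is small.

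Fourth, severe imbalance within workplaces is conditional on sizes that the article does not give. This also stands. It is likely with about ten or more small workplaces and rare with two or three large ones.

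Finally, sequential blocks in small workplaces can make later assignments guessable in an unblinded trial. This is a fair caution, and it decides which form of the fix is preferable.

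**Conclusion.** The point holds as a minor precision improvement. Allocation and analysis, as described, do not use workplace, although recruitment is organised by workplace. The treatment estimate stays unbiased and type I error stays near 5%.

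The power given up, compared with stratifying and adjusting, is about 0-2 points at an ICC of 0.05 or less, 2-4 at 0.10 and 6-7 at 0.20. These figures assume N = 90, ρ = 0.5, and 3 to 10 workplaces. The number of workplaces, their sizes and the ICC are all assumptions. With planned power of only about 0.80 there is little slack, but a low ICC would make the gain negligible.

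The tension with 57 per group arises only if the table is simple randomisation, and it does not threaten the trial.

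**What to change.** In 2.7, randomise within each company or institution. The preferable form is to allocate each workplace's consented group at once in equal halves. This fits the on-site gatherings and leaves no later assignment to predict. Otherwise, use concealed permuted blocks of varying size within workplace. Pool very small workplaces into one stratum. If this is already planned, say so in 2.7.

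In 2.13, include workplace by time in the T1-T2 analysis (equivalently, workplace as a factor in the model for change).

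Do not add the workplace term without stratifying. With many small workplaces and a low ICC this can lose a few points: 0.756 against 0.803 at K = 10 and ICC 0.02.

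The cost is slightly more list administration and a few degrees of freedom, at most about 1 power point if workplace has no effect on change. The allocation part has to be settled before the first participant is enrolled.
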